### Sample size {14}

#### Quantitative

The sample size for the PIRM study is based on a significance level of *p* = .05 and power *β* = 0.80. The expected effect size is Cohen’s *d* = .30 for the intervention groups based on differences between sum scores. In other words, we wish to detect a relatively small difference between enrollment in either of the parenting groups (factor 1) or in the addition of the MFS (factor 2). Based on this values, our aim is to recruit *N* = 360 families, *n* (IY, w/MFS) = 90, *n* (ICDP, w/MFS) = 90 , *n* (IY, no-MFS) = 90, n (ICDP, no-MFS) = 90. The study is powered to detect a relatively small effect size for main effects of either the parenting factor, IY_tot_ = 180 vs ICDP_tot_ = 180; or the MFS factor, MFS_tot_ = 180 vs no-MFS_tot_ = 180. Interaction effects between factors (e.g., IY w/MFS vs ICDP w/MFS) were not included in the power analysis due to the unknown nature of the main effects. With 6 families in each intervention group, the study would need roughly 5 municipalities to run two intervention groups, twice per year for 3 years.

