## Assignment of interventions: allocation

### Sequence generation {16a}

A project analyst at the primary site who does not have contact with sites or families will do the allocation of the factorial conditions using a random number sequence where groups at each site are assigned an ID and then each ID is assigned either to condition 1 (w/MFS) or 0 (no-MFS) (stage 1 randomization). A second list of IDs representing families is also randomized (stage 2) to condition 1 (IY) or 2 (ICDP). To understand the randomization, it is important to understand that each site will conduct both an IY and ICDP parenting group concurrently, so that families can be randomly assigned to either group. However, sites are not capable of running four unique groups concurrently (i.e., IY w/MFS, IY no-MFS, ICDP w/MFS, ICDP no-MFS). Therefore, randomization occurs in two stages. Stage 1 randomly assigns the two groups at each site to the MFS condition (factor 2). For example, at site 1, the IY group is randomly assigned to the MFS condition, and the ICDP group is assigned to the no-MFS condition. The decision to randomize the MFS condition at the group level is practical: in order to use the MFS properly, the group leaders need to respond to the feedback. Therefore, any actions taken by the group leader will affect the entire group. In order to minimize systematic differences that may be introduced by group leaders, the groups will be re-randomized to the MFS condition when a new group begins, or roughly once per semester.

Stage 2 randomization is responsible for assigning families at each site to one of the two parenting conditions (i.e., IY or ICDP; factor 1). Stage 2 randomization by the primary site will occur after the T1 survey has been completed by the participating families.

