### Implementation {16c}

To preserve the factorial design, we need to randomize to four conditions (see table in the “Trial Design” section of this document). We cannot randomize families to four separate conditions at each site, because this would require running four groups at each site every semester (see also the “Sequence generation {16a}” section). It would not be feasible for the municipalities to conduct four groups in parallel due to the staffing requirements. Therefore, randomization in PIRM has two stages: stage 1, randomization to MFS condition at the group level, and stage 2, randomization of families to IY or ICDP parenting groups.

Recruitment of families at each site will be ongoing. Families will be randomized when (a) a maximum of 12 families are recruited or (b) a cutoff date is reached each semester. The cutoff date will be established by the amount of time it takes to complete a group, (i.e., 15 weeks for IY, 12 weeks for ICDP). In Norway, summer holidays usually occur between June and August; therefore, groups must have adequate time to finish within the time period from January to June or late August to December.

The parenting groups (2 per site) are randomly assigned to one of the MFS (Y/N) conditions so that one group at each site will be in the MFS conditions. For example, at site 1, the ICDP group is randomly assigned to the MFS condition during the first semester. The following semester the groups will be reassigned and the IY group at site 1 may end up in the MFS condition.

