## Statistical methods

### Statistical methods for primary and secondary outcomes {20a}

We will conduct analyses in a longitudinal framework, controlling for scores at baseline. For example, to test the primary outcomes of the effectiveness study, we will use linear mixed modeling to assess changes in parenting or child behavior in the different intervention groups while controlling for scores pre-intervention. The analyses will account for independence within the respondents (time as a random effect) as well as group membership, because the randomization to the MFS condition is at the group level. We will also look at interactions between main effects given enough power, for example, between the MFS conditions (factor 2) and the parenting conditions (factor 1).

See the “Outcomes {12}” section for description of qualitative analysis.

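### The programme-by-MFS interaction can be estimated only between site-semesters, and the planned model does not name site-semester

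*Protocol article*

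**What the plan says.** All references are to the protocol article.

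- **Sequence generation {16a}** and **Implementation {16c}**: each site runs an IY and an ICDP group at the same time, and families are randomised between them. MFS is allocated at group level, "so that one group at each site will be in the MFS conditions". The allocation is redrawn about once per semester. Four concurrent groups per site are ruled out as infeasible.
- **Sample size {14}, Quantitative**: the inputs are a "significance level of *p* = .05 and power *β* = 0.80" and d = 0.30, giving N = 360 with 90 families per cell. The layout is 6 families per group, about 5 municipalities, two groups each, twice a year for 3 years. "The study is powered to detect a relatively small effect size for main effects of either the parenting factor" or the MFS factor. On interactions: "Interaction effects between factors (e.g., IY w/MFS vs ICDP w/MFS) were not included in the power analysis".
- **Statistical methods {20a}**: a linear mixed model accounts for respondent and group membership. Then: "We will also look at interactions between main effects given enough power". No criterion for sufficient power is given, and site-semester is not mentioned.

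**The concern.** With one MFS group per site-semester, the only possible pairs are {IY+MFS, ICDP without MFS} and {IY without MFS, ICDP+MFS}. Both groups in a site-semester therefore have the same value of the interaction term. Anything shared by families at one site in one semester cancels from the main effects but stays in the interaction. The article presents the two-stage scheme as preserving the factorial design and does not mention this cost.

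Three things follow.

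- A model with group membership as its only cluster level gives wrong standard errors: too small for the interaction, too large for the main effects on which the trial is powered.
- Making the analysis depend on unspecified power leaves open when it will be done and how it will be read.
- The sample size section's illustration, IY with MFS against ICDP with MFS, is a simple effect of programme among MFS families, not an interaction. Those two cells never run together at a site.

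**Working it through.** **The plan's own figure.** n per arm = 2(1.960 + 0.842)²/0.30² = 174.4, so 175 per arm and 350 in total (two-sided 5%, 80% power). At 180 per arm the power is 0.81. N = 360 is reproduced for main effects.

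**Layout.** 5 sites × 2 semesters × 3 years = 30 site-semesters, 60 groups and 360 families at 6 per group.

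**Structure.** Code IY/ICDP and MFS/no-MFS as +1/−1. The product is +1 for both groups under one pairing and −1 for both under the other. With 30 site-semesters as fixed effects, the design matrix has 33 columns and rank 32, and the missing rank is the interaction. With sites as fixed effects (8 columns, rank 8), or with random effects, it is estimable.

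**Precision of the interaction.** The total variance is 1: vs for site-semester, vg for group, and ve = 1 − vs − vg. The documents give no intraclass correlations, so vs and vg are assumed.

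- Variance of a site-semester mean: Vb = vs + vg/2 + ve/12.
- The interaction (difference of differences) is twice the difference in mean between the two pairings. With 15 site-semesters each, SE = 2√(2Vb/15).
- Detectable at 80% power = SE × (2.048 + 0.855), on t with 28 df.
- If all four cells ran in every site-semester, vs would cancel: SE = √(4(vg + ve/6)/15).

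| vs = vg | Vb | SE | Detectable | Power for 0.30 | Detectable, four cells per site-semester |
|---|---|---|---|---|---|
| 0 | 0.083 | 0.211 | 0.61 | 28% | 0.61 |
| 0.02 | 0.110 | 0.242 | 0.70 | 22% | 0.64 |
| 0.05 | 0.150 | 0.283 | 0.82 | 18% | 0.67 |
| 0.10 | 0.217 | 0.340 | 0.99 | 14% | 0.72 |

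The first row's SE equals 4/√360 = 0.211, that of any balanced 2x2 with 360 families.

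A simulation analysing site-semester means (4,000 runs per setting) recovered a true interaction of 0.60 as 0.600 at variances of 0.02 each. At a true value of zero and variances of 0.05 each, type I error was 0.054.

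**Effect of leaving site-semester out.** A model with group as the only cluster level absorbs vs into the group variance.

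- Interaction SE: √(4(vs + vg + ve/6)/15), against the correct 2√(2Vb/15).
- Main-effect SE: √(2(vs + vg + ve/6)/30), against the correct √(2(vg + ve/6)/30).

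| vs = vg | Interaction SE: group only / correct | Main-effect SE: group only / correct |
|---|---|---|
| 0.05 | 0.258 / 0.283 | 0.129 / 0.115 |
| 0.10 | 0.298 / 0.340 | 0.149 / 0.125 |

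For the interaction, the nominal 5% test becomes about 2(1 − Φ(1.96 × 0.258/0.283)) = 7.4% at 0.05 each, and 8.6% at 0.10 each.

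**Gain from pairing semesters.** Assume lasting variances of 0.04 for site and 0.04 for leader team (one team per programme at each site), with ve = 0.92.

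- Interaction SE falls from 2√(2(0.04 + 0.02 + 0.92/12)/15) = 0.27 to 2√(2(0.92/12)/15) = 0.20.
- MFS main-effect SE falls from √(2(0.04 + 0.92/6)/30) = 0.114 to √(2(0.92/6)/30) = 0.101.

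Variance specific to one semester is not removed, so the real gain could be smaller.

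**The case against.** The design is deliberate and sensible. Four concurrent groups are not feasible, and keeping both main effects within site-semester while the unpowered interaction falls between them is a standard choice. The protocol claims no power for the interaction: it excludes it from the sample size and makes the analysis conditional. Most of the imprecision comes from N = 360 and not from the two-cell structure. At variances of 0.05 each, the structure moves the detectable interaction only from 0.67 to 0.82 SD. All of this stands.

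Four stronger readings are tempting, and the documents do not support them.

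- **That the interaction is aliased.** This holds only with fixed site-semester effects, which the plan does not specify. Because pairings are redrawn each semester, the contrast is estimable and unbiased; site and calendar differences add noise.
- **That it can never have enough power.** For an interaction of 0.90 SD, power is 72 to 98% over the variances tabulated.
- **That the two randomisation sections contradict each other.** The clause "groups at each site are assigned an ID and then each ID is assigned either to condition 1 (w/MFS) or 0 (no-MFS") could be read alone as independent assignment of each group. The same paragraph's example has one group with MFS and one without, which agrees with the implementation section.
- **That a null interaction will be used to justify pooling.** The protocol does not say so.

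One could also leave the random-effects structure to the analysis plan. But the article does name the cluster levels it will account for, and the level that carries the interaction is absent.

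**Conclusion.** The point holds in a limited form. The programme-by-MFS interaction is an unbiased but imprecise contrast between site-semesters. The protocol does not acknowledge this, and its stated model omits that level. The detectable interaction is 0.61 SD without clustering and about 0.7 to 1.0 SD at the assumed variances, with 14 to 28% power for an interaction as large as the planned main effect. The omission also costs precision on the main effects wherever site-semesters differ.

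The figures assume 30 site-semesters split 15/15 between pairings, 6 families per group, no dropout, no gain from baseline adjustment, and variances of 0 to 0.10 that the documents do not give. The main-effect estimates are not biased by any of this, and the sample size calculation as stated is reproduced. The change is worth making because it is cheap.

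**What to change.** 1. **Model.** Add site-semester as a random effect alongside respondent and group membership. This corrects the standard errors of the interaction and both main effects at no cost. If item 2 is adopted, also include terms for site and for programme within site, so that the reported standard errors reflect the pairing.
2. **Allocation for the remaining semesters.** Assign the MFS pairing in permuted pairs of semesters within site, so that each site and leader team gets both pairings equally. This also serves the stated aim of limiting group-leader differences. The cost is a new random list. The drawback is that the second semester's pairing becomes predictable to group leaders, contrary to Concealment mechanism {16b}. Little harm should follow, because families are randomised to programme after T1. It helps only where a site stays for both semesters.
3. **Wording.** Define the interaction as (IY+MFS − IY) − (ICDP+MFS − ICDP), and replace the example in the sample size section. In place of the power condition, state that the interaction is a between-site-semester contrast, exploratory, and reported with a confidence interval. This costs a few sentences.

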### Interim analyses {21b}

No plans for interim analyses exist at this time.

### Methods for additional analyses (e.g., subgroup analyses) {20b}

Sub-groups analyses will be performed in a mixed methods modeling framework. Some of the sub-groups analyses will be determined based on factors at baseline, such as language or country of origin. Actual sub-groups will be dependent on the characteristics of the recruited sample.

### Methods in analysis to handle protocol non-adherence and any statistical methods to handle missing data {20c}

We will analyze the quantitative data in an ITT approach. We intend to use full information estimates (e.g., maximum likelihood) or multiple imputation to include cases that may have missing data [32, 33]. This approach introduces less bias into analyses than other approaches (e.g., listwise deletion, regression imputation, etc.).

### Plans to give access to the full protocol, participant level-data, and statistical code {31c}

Project coordinators and scientists will have access to the data via remote desktop environment in TSD. The data will be anonymized by removing secondarily-identifying information after the study and research period is ended. This dataset will be made public in accordance with research practices at UiT The Arctic University of Norway.

## Oversight and monitoring

### Composition of the coordinating center and trial steering committee {5d}

Data will be monitored by staff at the host organization and the researchers on the study. Regular examination of the data will be conducted to assess integrity and address possible data collection issues.

### Composition of the data monitoring committee, its role and reporting structure {21a}

The DMC will be comprised of people who are internal and external to the project; however, all will be employed with the host organization or its project collaborators. This team will be responsible for maintaining data integrity and reporting anomalies to the project group.

### Adverse event reporting and harms {22}

The interventions in this study are not expected to do harm; however, all interventionists are part of the mental healthcare system and have local protocols to which they must adhere in the course of their work.

### Frequency and plans for auditing trial conduct {23}

There is no plan for auditing trial conduct outside of the existing systems that are responsible for audits, such as funders or ethics committees.

### Plans for communicating important protocol amendments to relevant parties (e.g., trial participants, ethical committees) {25}

Changes to the protocol are communicated to the funding agency as they occur and during our annual reports. Protocol changes that are directly relevant to participants are communicated through the contact personnel at the participating research sites, as they have direct contact with the participants.

### Dissemination plans {31a}

Project results will be communicated through scientific conferences; peer reviewed, scientific journal articles; popular publications; project and affiliated webpages; and Ph.D. dissertations. As part of the agreement for grant funding, all scientific journal publications will be open access.

## Discussion

The PIRM study takes place within the context of recent requirements for refugee families to participate in parenting programs. The knowledge gained regarding effects of the parenting interventions will further inform policymakers regarding the use of these programs for families with refugee background. Our results will further provide guidance about the use of a weekly measurement and feedback within the context of these interventions. This guidance will evaluate the effectiveness of MFS with parenting interventions, as well as its feasibility of implementation in first-line preventive services.

## Trial status

This is the 2nd version of the study protocol, completed in February 2020. The first participants were recruited in September 2020. Recruitment will continue until the second half of 2023.

Contact for the public and scientists regarding the status of the study can be addressed to Associate [name] at [contact] or via email at [contact]. The mailing address for the project is as follows: UiT Norges arktiske universitet, Det helsevitenskapelige fakultet, RKBU Nord, [name].

## Abbreviations

ECBI: Eyberg Child Behavior Inventory
ICDP: The International Child Development Program
IG: Intervention Goals
IY: The Incredible Years Basic Parenting Program
MFS: Measurement and Feedback System
P-MFS: Parenting Measurement and Feedback Scale
PPI: Parenting Practices Inventory
PSI: Parent Stress Index-Short Form
READ: Resilience measure
RKBU: The Regional Center for Child and Adolescent Mental Health and Child Welfare
SESBI: Sutter-Eyberg Student Behavior Inventory-Revised
TSD: Services for Sensitive Data, University of Oslo
